### Study timeline

Trial start: January 2017.

Start of baseline data collection and intervention in general practice: March 2017.

End of intervention in general practice: March 2018.

End of 12-month follow-up data collection: May 2018.

Start of data analysis: June 2018.

Planned study end date: December 2018.

Duration: 2 years.

### Harm

The intervention is safe although we will closely monitor unintended consequences through the e-MPODERA platform with the help of the moderator. Risks arising from participation are considered to be very low. The proposed interventions are already offered to patients throughout Spain and internationally. The only difference conferred by participation is that the intervention will be randomly allocated and more carefully assessed.

## Discussion

Conceptual and practical approaches to patient empowerment have developed exponentially over the past decade and reflect a shift away from paternalistic perceptions of the professional-patient relationship and towards an interactional-model approach centred in equity and collaboration, according to the bioethical principle of autonomy [34].

In this study we will assess whether participation in the e-MPODERA virtual COP improves the attitudes of primary healthcare professionals to the empowerment of patients with chronic diseases. We will also assess whether this change in the attitude of healthcare professionals will enhance patient empowerment.

### Study strengths and limitations

Currently — and despite the importance of maintaining the knowledge and skills of healthcare professionals — conventional approaches to continuing professional development (lectures, meetings) seem insufficient to translate learning to practice [35, 36]. We will experimentally test an innovative learning intervention based on a COP in the field of patient empowerment, for which the literature lacks experimental evaluations. This project, furthermore, proposes a COP in a virtual format, using technology to facilitate communication between COP members in different geographic locations and even different time zones, thereby increasing the diversity of the network [37].

A virtual COP offers theoretical and tangible benefits for improving professional knowledge and implementation in clinical practice [37], as follows:It is a unique, dynamic, semi-structured system set within an environment of continuous learning and offering immediate access to a broad range of knowledge.It offers access to repositories of current or historical discussions (archived knowledge) and enables access to peer or senior professionals regarding the application of appropriate knowledge in practice.It acts as a common platform for the discussion and exchange of ideas and resources (documents, data, audio files, videos, etc) aimed at ensuring optimal patient care.

Many training activities in the healthcare sector are currently designed for only one discipline or profession and so do not address the need for the perspective of inter-professional teams practising in these systems or settings [38–40]. In the experience of healthcare professionals, it appears that interacting with peers fosters learning and information sharing [16]. The e-MPODERA project will facilitate such inter-professional interactions.

We will run the clinical trial in three regions that are broadly representative of the Spanish national healthcare system, with publicly funded care models and different healthcare management models. Primary healthcare professionals across Spain — mainly GPs and nurses — have similar curricula (in terms of degrees and diplomas) and the GP specialization is based on similar training programmes. During the trial we will only allow the selected PCPs access to the COP, so as to limit the “viral” potential of the COP. Opening a second phase of open-access COP will control this limitation.

In similar experiences [41], the participation rate has been low, with just 30% of professionals accepting the invitation and only 3% becoming active in the COP. Therefore, we calculated the data sample so as to reduce the risk of a low participation rate that would render it difficult to attribute any change in PPOS and PAM scores to the e-MPODERA intervention. To enhance participation in the COP, we will implement several strategies, including an active role by a community manager, weekly emails as reminders that summarize the most important issues of the week with relevant information attached and a competitive score system according to the goals achieved.

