**Methods:**

This paper describes the protocol for a cluster randomized controlled trial. We will randomly assign 18 primary-care practices per participating region of Spain (Catalonia, Madrid and Canary Islands) to a virtual community of practice or to usual training. The primary-care practice will be the randomization unit and the primary healthcare professional will be the unit of analysis. We will need a sample of 270 primary healthcare professionals (general practitioners and nurses) and 1382 patients. We will perform randomization after professionals and patients are selected. We will ask the intervention group to participate for 12 months in a virtual community of practice based on a web 2.0 platform. We will measure the primary outcome using the Patient-Provider Orientation Scale questionnaire administered at baseline and after 12 months. Secondary outcomes will be the sociodemographic characteristics of health professionals, sociodemographic and clinical characteristics of patients, the Patient Activation Measure questionnaire for patient activation and outcomes regarding use of the virtual community of practice. We will calculate a linear mixed-effects regression to estimate the effect of participating in the virtual community of practice.

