### Sample size

We calculated the required number of primary healthcare professionals for the purpose of comparing two independent means, considering as significant a post-intervention mean difference of 0.2 points and a common standard deviation of 0.5 points in the PPOS questionnaire between the e-MPODERA virtual COP intervention and control groups [29]. Each group will need 100 professionals, assuming alpha error of 0.05 and power of 80%. Since we will randomize by clusters, we have adjusted the sample size to take into account the design effect. Considering an intraclass correlation coefficient of 0.03 and assuming an average size per cluster of five healthcare professionals, we obtained a design effect of 1.12 [30]. Given these assumptions and expecting 20% loss to follow up after 12 months, we calculated a sample size of 270 healthcare professionals (135 professionals per group). The recruited healthcare professionals will, in turn, recruit a total of 1382 patients (assuming 20% loss to follow-up), the number that is required to detect a mean difference between the two groups of 4 points in the Patient Activation Measure questionnaire (PAM) scale [28].

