### Data collection, management and analyses

We will collect a mixture of professional and patient-reported data, using validated questionnaires for the primary and most of the secondary outcome measures. We will require each recruiting site to keep accurate and verifiable source notes regarding each participant’s inclusion and continued participation in the study. We will collect, transfer and store data in accordance with Good Clinical Practice (GCP) guidelines and data protection requirements. The e-MPODERA standard operating procedures (SOPs) and study data management plan will define the exact procedures for collecting, transferring, storing and quality-controlling study data.

We will perform descriptive and exploratory analyses, including cluster analyses according to participant baseline characteristics, using means and standard deviations for continuous variables and proportions for categorical variables. We will compare the two groups in terms of PPOS scores, PAM scores and descriptive variables. We will perform inferential analysis using the Mann-Whitney U test — with a 95% confidence interval — to compare across-group results in the PPOS and PAM tests in terms of score at 12 months from baseline.

We will perform a multilevel analysis of models for the main outcome (the PPOS test), where the response variable will be the difference between initial and final scores in the questionnaire administered to participating professionals and the explanatory variable will be the dichotomous intervention variable (1 = COP/0 = control). This model considers covariates such as age, sex and professional profile and also takes into account the random effect associated with the COP. We will use the propensity score to control for possible selection bias and enhance the accuracy of the model.

We will perform intention-to-treat analyses using the statistical software (http://www.R-project.org/) and PASW Statistics 18. We will use the last observation carried forward to impute missing data and will report analyses with and without imputation. We will inform participants that they can leave the study at any time. We will report missing data, if applicable, by categorizing the participants as follows: mistakenly randomized, did not receive the intervention, withdrew consent, crossed over, dropped out, did not adhere, lost contact or other reasons not specified [33].

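### The sample size is said to guard against low use of the virtual community of practice, but the calculation contains no allowance for it, and the abstract describes an allocation effect as an effect of participating

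*Protocol article*

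**What the plan says.** The Study strengths and limitations section reports uptake in similar experience, "with just 30% of professionals accepting the invitation and only 3% becoming active in the COP", and continues: "Therefore, we calculated the data sample so as to reduce the risk of a low participation rate". It then lists engagement measures: a community manager, weekly reminder emails and a competitive scoring system.

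The Sample size section gives the only calculation for professionals. It starts by "considering as significant a post-intervention mean difference of 0.2 points" between the intervention and control groups, with "a common standard deviation of 0.5 points in the PPOS questionnaire", alpha 0.05 and 80% power, giving 100 per group. It then applies an intraclass correlation of 0.03 with five professionals per practice (design effect 1.12). The last step reads "Given these assumptions and expecting 20% loss to follow up after 12 months" and arrives at 270 professionals, 135 per group. The patient figure of 1382 also mentions only 20% loss.

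Use of the COP is voluntary once a practice has been allocated to it (Intervention section). Under Data collection, management and analyses, the explanatory variable is the allocated arm (1 = COP, 0 = control), and "We will perform intention-to-treat analyses". The Abstract, however, says the mixed model is fitted "to estimate the effect of participating in the virtual community of practice", and the opening of the Discussion likewise speaks of testing whether participation changes attitudes.

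**The concern.** The article names low participation as a main risk to the trial and tells the reader that the sample size was set with that risk in mind. The published calculation has no term for participation, adherence or a diluted effect. Loss to follow-up cannot stand in for it. A professional who never opens the platform but returns the 12-month questionnaire is not lost; under intention to treat that person stays in the COP arm and pulls its mean towards the control mean. Inflating for loss restores the number analysed. It does not restore the size of the effect.

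Two things are at stake. Readers may credit the trial with a protection that its calculation does not provide. And because use is voluntary, the effect of being offered the COP and the effect of taking part in it are different quantities. The planned model estimates the first, while the Abstract and Discussion name the second, so a null result could be reported as evidence about participation when it may reflect non-use.

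**Working it through.** **Inputs.** Difference 0.2, SD 0.5, alpha 0.05 (taken as two-sided, which reproduces the stated figure), power 80%, intraclass correlation 0.03, cluster size 5, loss 20% (Sample size); 54 practices (PCP recruitment); items scored 1 to 6 and averaged (Primary outcome); 30% and 3% (Study strengths and limitations).

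**Step 1: reproduce the 270.**
- Two-sample t calculation for 0.2 with SD 0.5: 100 per group, as stated.
- Design effect: 1 + (5 − 1) × 0.03 = 1.12, as stated.
- 100 × 1.12 = 112; 112 × 1.2 = 134.4, rounded up to 135 per group, 270 in total, as stated.

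The stated inputs use up the whole sample. The clusters leave no reserve either: 54 × 5 = 270. (Dividing by 0.8 instead of multiplying by 1.2 would give 112 / 0.8 = 140 per group, 280 in total. That is a side matter worth about two points of power, 79% against 81%.)

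**Step 2: power of the planned sample at the full 0.2.** Effective number per arm after 20% loss and clustering: 135 × 0.8 / 1.12 = 96.4. Standard error: 0.5 × √(2 / 96.4) = 0.072. Power: Φ(0.2 / 0.072 − 1.96) = Φ(0.82), about 79%.

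**Step 3: bring in participation.** Let p be the share of COP-arm professionals who use the platform, and assume that non-users gain nothing. The intention-to-treat difference is then p × the effect in users. The article does not say which of these the 0.2 is meant to be, so both readings are shown. They are alternatives.

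| Participation p | Reading A: 0.2 is the intention-to-treat difference; required effect in users = 0.2 / p | Reading B: 0.2 is the effect in users; intention-to-treat difference = 0.2 × p | Power under B |
|---|---|---|---|
| 100% | 0.20 | 0.20 | 79% |
| 80% | 0.25 | 0.16 | 60% |
| 50% | 0.40 | 0.10 | 28% |
| 30% | 0.67 (0.67 / 0.5 = 1.3 SD) | 0.06 | 13% |
| 3% | 6.7 | 0.006 | about 5%, the alpha level |

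Under A, power stays at about 79% in every row, because the intention-to-treat difference is fixed; what changes is how much users must gain. At 3% the required 6.7 points exceeds the 5-point span of a 1-to-6 scale.

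Under B, holding 80% power would multiply the sample by 1 / p²: 4 times at 50% and about 11 times at 30%.

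Under neither reading do the stated inputs make provision for uptake as low as the cited rates.

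**The case against.** The strongest reply is that the 0.2 is worded as a difference between the two groups and the analysis is by intention to treat. The natural reading is therefore A, and power is about 79%. This stands. A reader might infer from the right-hand columns that the trial's power collapses; the article does not support that as a flat statement, because it nowhere says that 0.2 is the effect in users only.

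The cited rates may also not carry over. The 30% is acceptance of an invitation in another setting, whereas here professionals volunteer and consent before randomization. The 3% is active membership, and someone who only reads the newsletters or articles may still gain something. The Randomization section chose practices as clusters because of possible contamination among professionals, so a non-user may learn from a colleague, and zero effect in non-users is doubtful. The engagement measures may raise use. All of this stands, and it makes the rows for 30% and 3% illustrations of the rates that the article itself cites, not forecasts.

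A reader might also infer that the plan is deficient because it names no analysis separating an ineffective COP from an unused one. That does not follow. The Abstract lists outcomes on use of the COP, missing-data reporting will include categories for not receiving and not adhering to the intervention, and a supportive complier analysis is commonly left to an analysis plan, which is not at hand.

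Finally, *participating* in the Abstract may be only loose wording, since the model is explicit about the allocated arm. That limits the harm to interpretation, but the wording still names the wrong quantity.

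None of these replies puts a participation term into the calculation.

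**Conclusion.** The point holds as a mismatch between what the article claims for its sample size and what it calculated. That part needs no assumption: the stated inputs reproduce 270 exactly and leave nothing over for low participation.

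The size of the consequence depends on what 0.2 means. As an intention-to-treat difference it keeps about 79% power, at the price of an effect in users of 0.40 points at 50% participation, 0.67 at 30%, and an impossible value at 3%. As an effect in users, with none in non-users, it gives about 60%, 28% and 13% power at 80%, 50% and 30%. The second set is conditional on an assumption that the article does not state, and should not be quoted without it.

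The description of the model in the Abstract and the opening of the Discussion should be brought into line with the allocated-arm, intention-to-treat analysis. The planned sample and the primary analysis need not change on account of this point.

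**What to change.** 1. In Study strengths and limitations, delete the sentence claiming that the sample was calculated with low participation in mind, or correct it to say that the calculation allows for clustering and loss to follow-up only. The engagement measures can stay as the response to the risk.
2. In Sample size, state whether 0.2 is the intention-to-treat difference averaged over all allocated professionals, or the effect in users. Give only the table that matches: the implied effect in users by participation in the first case, or intention-to-treat power by participation in the second. Giving both would mix two definitions, since power at a fixed intention-to-treat difference does not vary with participation.
3. In the Abstract and the opening of the Discussion, describe the model as estimating the effect of allocation to, or being offered, the COP.

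Optionally, add a supportive complier-average analysis with allocation as the instrument, platform-use data as exposure and standard errors clustered by practice. It would need the caveat that spillover within practices threatens its exclusion restriction. Its absence is not a defect.

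The cost is a few sentences and one small table, with no new data collection. The price is candour: the article would have to state either the large gain it expects in users or the lower power it has if uptake is poor.

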## Trial status

Recruitment commenced in November 2016 and is ongoing at the time of submission.

## Abbreviations

COP: Community of practice
e-MPODERA: Effectiveness of a Virtual Intervention to Improve Healthcare Professional Attitudes to Patient Empowerment
GCP: Good Clinical Practice
GP: General practitioner
PAM: Patient Activation Measure
PCP: Primary-care practice
PI: Principal investigator
PPOS: Patient-Practitioner Orientation Scale
SOP: Standard operating procedure
